## 2. Research Methodology

### 2.1. Study Overview and Design

WaSH in Manila Schools was a research project aimed at improving children’s environmental health by addressing inadequate school WaSH and promoting health literacy and hygiene practices (Figure 2). We implemented the project from January 2017 to February 2019, first conducting an observational study [27] to assess the WaSH situation in 15 public schools in Metro Manila, and then conducting a longitudinal study to develop, implement, and evaluate WaSH interventions in the same public schools (Figure 2). We conducted a cluster-RCT to address three specific aims (Figure 2) and compare the efficacy of four school-based WaSH intervention packages. Each intervention package consisted of different combinations of four elements: (1) WaSH policy reinforcement, (2) health education, (3) hygiene supplies, and (4) WaSH facilities (e.g., toilets, urinals, handwashing basins) improvements (Table S1).

This was a two-arm cluster-RCT (Figure S1), with one intervention arm and one control arm. The control arm received no intervention, rather the “standard of care”, which we defined as WaSH policy reinforcement, a hygiene workshop for teachers, and two health education sessions. The intervention arm was further divided into four groups (A, B, C, and D), based on the volume (low, medium, or high) of health education provided. Cluster units were public schools located in three cities of Metro Manila, Philippines, where many people, including a majority of public school children, were exposed to inadequate WaSH.

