#### 2.5.3. Baseline Survey and Randomization

At baseline, we conducted a four-part school-based survey (Figure S3) to measure: (1) children’s health literacy and nutrition status; (2) handwashing prevalence; (3) school restrooms’ WaSH adequacy; and (4) schools’ WaSH policies. We developed a self-administered health literacy questionnaire for children in English and then translated it to Tagalog (Filipino language) (Tables S3 and S4). We made one version for primary and one version for secondary school children. The QuickTapSurvey^©^ app (Formstack LLC, Fishers, IN, USA), installed on password-protected tablets and smartphones, was used to administer all survey instruments. It is a cloud-based data collection tool that allows for simultaneous offline data entry and stamping with global positioning system (GPS) coordinates, date, and time. We applied validation rules and range limits for precise data entry.

The research supervisor conducted a full-day (8 h) initial training workshop (Table S7) for research assistants before conducting school surveys. Each school survey was conducted by a team of 5–7 rotating research assistants, directly managed by the research supervisor. To begin the school survey, we first explained the study’s aims, objectives, and methods to the children in Tagalog (Figure S3). We emphasized that participation in our study was voluntary and anonymous, and that results would remain confidential and have no impact on anyone’s school grades. Children’s full name, date of birth, and telephone number were collected and stored in a separate Microsoft© Excel spreadsheet secured in password-protected tablets. Next, we assigned children unique identification (ID) numbers and gave them each three tickets that were printed with their ID number. The ticketing system was a quality control measure that ensured that all children provided all the requested data. Children were instructed to give one ticket to the assigned research assistant at every station that they visited during the school survey (Figure S3).

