After obtaining data from the children, research assistants completed the school restroom inspection checklist, took photos of WaSH facilities, and interviewed school principals or representatives, inputting all data into the app. We obtained school administrative data, e.g., budget for maintenance and other operating expenses, from the DepEd. At the end of each workday, research assistants discussed their work with each other, shared lessons learned, and identified areas for improvement. Upon accessing an internet hotspot, we used the app to transmit anonymized data to a central database via cloud storage. Research assistants periodically checked uploaded data to verify the completeness of data upload and identify discrepant, missing, or duplicate data. When needed, appropriate remedial action was taken, e.g., re-training research assistants or clarifying instructions for children.

After completing baseline surveys, we assigned two schools to the control arm and 13 schools to the intervention arm (Figure 3). We purposefully assigned two schools to the control arm because one school had a school principal who directly asked us to participate in our previous observational study. The other school was integrated (offering all possible grade levels, from kindergarten to grade 12) and was the location where we had pilot-tested our survey instruments before the observational study. We randomly allocated schools in the intervention arm to one of four groups. One research assistant and the research supervisor conducted randomization in Microsoft^©^ Excel as follows: (1) In one column, we listed the names of the 13 schools in the intervention arm, with one row representing one school. (2) In another column, we listed the four intervention groups (A, B, C, and D), with one row representing one group. We previously determined how many schools would be allocated to each group (Table S1). (3) In a third column, we used Excel’s random number function and ranked the schools, assigning each school to either group A, B, C, or D (Table S1). Except for the research supervisor, all research assistants, study participants (children), school personnel, and parents were blinded to the assignment of schools to the intervention arm and subsequent random allocation to intervention groups A–D.

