At the core of our intervention was health education. Research assistants conducted interactive verbal presentations for children, who, depending on which intervention group they belonged to, received two to four health education sessions that lasted one hour each. The content of the health education sessions (Figure S5) was based on the existing DepEd curriculum and open educational resources from, e.g., the United States Centers for Disease Control and Prevention (CDC) and Environmental Protection Agency (EPA). Microsoft^©^ PowerPoint slides, with visually appealing graphics to attract children’s attention, were created (Figure S5). Each health education session included a brief lecture, class discussion, and a trivia game. We also incorporated role-playing, other games, and singing the “Happy Birthday” song to teach children the correct duration of time for handwashing. Besides health education sessions, we used mixed methods to pique children’s interest, invite active participation, and encourage a sense of empowerment about hygiene at the personal- and environment-levels. For example, we implemented poster-making and school restroom-cleaning contests, as well as songwriting workshops specifically for children and adolescents from secondary schools. Research assistants also developed an original educational video, filmed in Tagalog, called “Hygiene Heroes”, to promote proper handwashing (Film S1). After launching the intervention, we promoted adherence with various communication strategies (Table S8).

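### The statement that all research assistants were blinded conflicts with their role in randomisation and group-dependent delivery, so blinded assessment of observed handwashing and restroom adequacy cannot be claimed as described

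*Protocol article*

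**What the plan says.** On blinding, section 2.5.3 of the protocol article says: "Except for the research supervisor, all research assistants, study participants (children), school personnel, and parents were blinded". What they were blinded to is the assignment of schools to the intervention arm and the later allocation to groups A–D. The supervisor is the only exception named.

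On allocation, the same paragraph says: "One research assistant and the research supervisor conducted randomization". The working sheet was not masked: "we listed the names of the 13 schools in the intervention arm, with one row representing one school".

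On delivery, section 2.6 says: "Research assistants conducted interactive verbal presentations for children, who, depending on which intervention group they belonged to, received two to four health education sessions". Section 2.1 describes what the control arm received, "which we defined as WaSH policy reinforcement, a hygiene workshop for teachers, and two health education sessions".

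On outcome assessment, section 2.5.3 says: "Each school survey was conducted by a team of 5–7 rotating research assistants, directly managed by the research supervisor". It makes handwashing prevalence one of the four parts of that survey and has research assistants complete the restroom checklist and interview principals. Section 2.5.1 makes observed handwashing a primary outcome, and section 2.5.2 makes observed restroom adequacy a secondary one. Section 2.5.4 repeats the baseline method at follow-up. Section 2.7.1 puts the supervisor on site during data collection, giving feedback as it happens.

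**The concern.** A reader who takes the blinding sentence at face value will credit the trial with assessors who did not know which schools received which package. That matters most where the recorded value depends on an observer's judgement: whether a child washed their hands, and whether a restroom was clean and functional. It matters less for the self-administered literacy questionnaire and for measured height and weight.

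The limitations in section 3 cover non-random assignment to arm, self-report, possible misclassification and multiplicity, but not assessor knowledge of allocation. The article also offers itself as a blueprint for later trials, so the statement may be copied.

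**Working it through.** The document gives no figure to reproduce. The check sets the statements side by side.

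1. **Randomisation against blinding (both in section 2.5.3).** One statement excepts only the supervisor. The other gives an assistant a sheet with 13 school names beside groups A–D. Whoever ranked that sheet saw the group of every intervention school and could infer that the remaining two of the 15 schools were controls. Reading the sentence as covering only the moment of allocation does not help, because that is the moment at which this assistant took part. The contradiction is direct and needs no inference.

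2. **Delivery against blinding (section 2.6 with section 2.1).** The control arm received two sessions and the intervention groups two to four.
   - An assistant giving a third or fourth session therefore knows that the school is not a control.
   - An assistant giving two sessions cannot tell from the count alone whether the school is a control or a two-session intervention school.
   - There are three volumes (low, medium, high) for four groups, so volume alone cannot identify every group.
   - Hygiene supplies and facilities improvements might reveal more, but their allocation by group is in Table S1, which is not shown.

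   Delivery thus unblinds some assistants for some schools, not all assistants for all schools.

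3. **Who observes (sections 2.5.3, 2.5.4 and 2.7.1).** The same staff category conducts the surveys, in rotating teams of 5–7, and inspects the restrooms. No role separation is described at baseline or follow-up. Assistants discussed their work with one another at the end of each day, and the acknowledged unblinded person managed the teams on site. These are routes by which knowledge of allocation could reach an observer. They do not prove that it did.

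4. **Which assessments are exposed (Table 2).** Section 2.5.3 places allocation after the baseline surveys. Restroom inspections are dated February–March 2017 and September–December 2018, so the first precedes the June 2017 start of the intervention and only the second is exposed. Handwashing observations are dated October 2017 and February–March 2018. Both fall after the June 2017 start given in section 2.6, so even the first handwashing round may have followed allocation.

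**The case against.** The strongest reply is that only the randomisation step is a flat contradiction and that everything about outcome assessment is inference. Much of this stands. A reader might infer that the people who delivered the programme also scored it, so that the observed outcomes were definitely assessed unblinded. The article does not say so: no section places the same individuals in both roles at the same school, teams rotated, and the observation procedure and visit itinerary are in Figure S3, which is not shown and could assign roles. A reader might also infer that delivery told assistants the group of every school. The two control sessions rule that out.

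Nor can the bias be given a number. Suppose true handwashing prevalence p is equal in both arms and a fraction e of non-washers is recorded as washers in intervention schools only. Recorded prevalence there is p + (1 − p)e. With p = 0.30 and e = 0.05, 0.10 or 0.15 this gives 0.335, 0.370 or 0.405, a spurious relative risk of 1.12, 1.23 or 1.35. With p = 0.20 the relative risks are 1.20, 1.40 and 1.60. Every input is assumed, the error runs one way only, and the observer must be able to tell control from intervention, which step 2 shows was not always possible. The figures show how such a bias would work and do not estimate it here.

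The reply does not rescue the sentence. By the article's own account at least one assistant was unblinded, and nothing shown keeps that assistant, or those delivering three or four sessions, away from outcome observation.

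**Conclusion.** The concern holds in a limited form. The blinding sentence is incorrect as written, since it claims for all research assistants a property that the described procedures do not give them. It follows that blinded assessment of handwashing and restroom adequacy cannot be claimed as described. It does not follow that these outcomes were in fact scored by people who knew the allocation. That depends on role assignments the article does not report.

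The verdict rests on two readings of the text: that the handwashing observation was carried out by the survey teams, as its place in the four-part survey implies, and that no separate assessor team existed, since none is mentioned. The size of any bias is unknown. The correction should be made because it changes how results on one primary and one secondary outcome may be interpreted.

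**What to change.** Replace the blinding sentence in section 2.5.3 with a statement of who knew the allocation. The list should include at least the supervisor, the assistant who randomised, and the assistants who delivered the larger packages. State also whether the handwashing observers and restroom inspectors were separate from these people, and whether the October 2017 handwashing round came before or after allocation was known.

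If the roles were not separate, report follow-up handwashing observation and restroom inspection as unblinded, observer-judged outcomes, limit the conclusions drawn from them, and add this to the limitations in section 3.

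Only if observer identity was recorded, add a sensitivity analysis that leaves out observations made by staff who delivered sessions at that school. Section 2.5.3 mentions location, date and time stamps but not the observer, so this may not be possible. With only two control schools, the exclusion could also remove much of the comparator, and the report should say so.

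Shifting weight to the height and body mass index z-scores is not advised, because it would re-rank primary outcomes after data collection in a retroactively registered trial.

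The cost is a wording change and, conditionally, one extra analysis. The downside is a less favourable risk-of-bias statement.

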#### 2.5.4. Follow-Up and Other Assessments

Eight months later, we conducted a follow-up assessment by implementing the same methodology (i.e., 4-part school-based survey) that we used at baseline (Figure S3) and measuring the same types of outcomes (e.g., children’s health literacy and nutrition status, handwashing prevalence, school restrooms’ WaSH adequacy, and schools’ WaSH policies). Nine months later (17 months after the first health education session), we conducted a household questionnaire for children (Table S5). Thus, we were able to assess risk factors at the individual-, school-, and home-levels (Table 2).

We expected the intervention to influence children’s knowledge, behavior, and health outcomes. We defined indicators of the intervention’s impact as changes in children’s primary and secondary outcomes. We measured the difference between outcomes from the eight-month follow-up and baseline. We compared differences between control and intervention arms. We collected samples for water quality testing from study schools and a separate sample of households (located in the school neighborhood) after post-intervention assessments, as previously reported [27].

### 2.6. Intervention

The four parts of the intervention were: (1) WaSH policy reinforcement, (2) health education, (3) hygiene supplies, and (4) WaSH facilities improvements (Table S1). We implemented the intervention over eight months, from June 2017 to February 2018 (Figure 2). The development of the intervention was informed by findings from our previous observational study and baseline survey, as well as inputs from research assistants with expertise in the local context and stakeholders, e.g., school principals, teachers, and janitors. We also conducted opinion polls with students. It was important for us to use participatory research methods that engaged stakeholders so that we could assess whether our intervention would be acceptable or sustainable after the research project ended.

School principals were presented with a research portfolio containing recommendations for enforcing existing WaSH policies (Figure S4). We conducted one-hour hygiene promotion workshops for teachers, explaining the importance of improving WaSH in schools to achieve the United Nations’ (UN) Sustainable Development Goal (SDG) 6 [41], related to WaSH, and complying with the DepEd’s Order No. 10 [40], related to WaSH in schools. The workshop was valuable for teachers because it helped them gain new ideas about how to present to children specific health education topics, and see how big of a role classroom activities play in achieving schools’ WaSH policy goals.

At the core of our intervention was health education. Research assistants conducted interactive verbal presentations for children, who, depending on which intervention group they belonged to, received two to four health education sessions that lasted one hour each. The content of the health education sessions (Figure S5) was based on the existing DepEd curriculum and open educational resources from, e.g., the United States Centers for Disease Control and Prevention (CDC) and Environmental Protection Agency (EPA). Microsoft^©^ PowerPoint slides, with visually appealing graphics to attract children’s attention, were created (Figure S5). Each health education session included a brief lecture, class discussion, and a trivia game. We also incorporated role-playing, other games, and singing the “Happy Birthday” song to teach children the correct duration of time for handwashing. Besides health education sessions, we used mixed methods to pique children’s interest, invite active participation, and encourage a sense of empowerment about hygiene at the personal- and environment-levels. For example, we implemented poster-making and school restroom-cleaning contests, as well as songwriting workshops specifically for children and adolescents from secondary schools. Research assistants also developed an original educational video, filmed in Tagalog, called “Hygiene Heroes”, to promote proper handwashing (Film S1). After launching the intervention, we promoted adherence with various communication strategies (Table S8).

### 2.7. Trial and Data Management

Our trial involved a non-invasive, non-pharmacological intervention that posed little risk to participants. Thus, we saw no need for trial steering or data monitoring committees, nor did we see a need for interim data analysis. The research supervisor, who was based at the University of the Philippines Diliman for the entire duration of the trial, led the day-to-day management of data. The research team conducted the trial according to protocol, as approved by ethics committees, to ensure the safety of study participants, maintain the trust of stakeholders, preserve data quality, and maintain the integrity of the project.

Research assistants collected data using password-protected tablets and smartphones offline. We uploaded the data daily to the secure QuickTapSurvey^©^ server, and then refreshed tablets and smartphones, deleting all data from the devices. We downloaded data from the QuickTapSurvey server as Microsoft^©^ Excel files, which eliminated the need for manual data entry and its associated risks for error. We manually inspected data for discrepancies and inconsistencies and addressed these according to the SOPs (Figure S3). We used key matching data (children’s date of birth and telephone number) to link data from children’s questionnaires with data from health examinations.

#### 2.7.1. Protocol Standardization and Data Quality Control

To ensure the standardization of research activities within and between cities, across all data collection periods, as well as within and between various teams of research assistants, we used SOPs and a detailed school visit itinerary (Figure S3). The research supervisor explained and demonstrated the SOPs and itinerary in English and Tagalog during an in-person training workshop with research assistants before conducting field research. The research supervisor verified research assistants’ comprehension by return-demonstration. The research supervisor directly oversaw data collection and provided onsite, real-time feedback, providing additional training as needed. Data quality was monitored regularly, and discrepancies were immediately discussed and resolved within the research team. Research assistants were encouraged to propose solutions and workflow improvements.

#### 2.7.2. Dissemination

We discussed preliminary results with project partners and provided research portfolios, containing a summary of results, policy recommendations, and outline for an action plan, to school principals for dissemination to schoolteachers, parents, and children. The research portfolio was valuable for school principals because it helped them to describe their school’s progress toward WaSH-related goals, set by the DepEd. In the Philippines, we presented our methods and summary of interventions to a non-government organization and an international organization. We presented preliminary results at international conferences. Full results will be reported in a forthcoming paper [25].

### 2.8. Statistical Analysis

Because our study contains multiple arms (1 control and 4 intervention arms), it is necessary to develop a strategy for conducting statistical analysis that takes into account the study’s 5 arms, parallel design, and unequal allocation ratio between control and intervention arms. We will use an adjustment method to control for type I error due to the study’s multiple-arm design. Because we simultaneously assessed multiple outcomes, we will need to adjust for a possible multiple comparisons effect. One possible adjustment method is the Benjamini–Hochberg procedure [42], which controls for the false discovery rate (10%). We used unequal allocation, making the intervention group larger than the control group, because we aimed to increase the precision of the intervention comparison. Also, we aimed to make the study more acceptable to study participants and researchers by decreasing the likelihood of being allocated to the control group and not receiving the intervention. Because we aim to know whether and how interventions differ, we will not use a single global test of significance, which would compare all groups simultaneously. Rather we will use a dose-response model to examine trends. We will conduct all analyses by using the originally assigned intervention status (i.e., intention to treat), comparing each intervention arm against the control arm.

We will examine the role of missing data in the interpretation of findings. If we find no statistically significant difference between children who were missing data and children who were not missing data for key outcomes, then we will conclude that data were missing at random (MAR), though not missing completely at random (MCAR). MAR means that all data, within groups defined by the observed data, had an equal chance of being missing, and that the reason why data were missing is due to a known characteristic of the data themselves [43]. In our study, the possible reasons for MAR will likely be: nonresponse (some children did not answer all of the questions in the questionnaire) or loss to follow-up due to school absence or discontinued school enrollment because of drop-out, graduation, or relocation. On the other hand, MCAR will less likely be found in our study because it means that all data had an equal chance of being missing and that the reason why data were missing is not due to the data themselves [43]. In field research, this may be an unrealistic occurrence. We will consider using multiple imputation (MI) or full information maximum likelihood (FIML) to handle MAR data. An advantage of FIML is that it uses all available data provided by a given study participant. We will use Stata, version 15 (StataCorp., College Station, TX, USA), for all data analyses.

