### 1.2. Objectives

The WaSH in Manila Schools Trial aimed to identify an intervention that could better improve children’s health. Our conceptual framework (Figure 1) depicts our pre-specified hypotheses (Figure 2). To test our hypotheses, we will compare a comprehensive school-based WaSH intervention with no intervention, rather the “standard of care”. This comparison will enable us to estimate a potentially achievable reduction of inadequate WaSH, as well as estimate impacts on malnutrition reduction. Through our description of exposure-response relationships in Metro Manila schools, we will be able to provide estimates of the range of improvements that can be achieved in real-world, LMIC conditions where elements of adequate school WaSH, including improved sanitation, are typically combined with inadequate school WaSH and unimproved sanitation. Results of the trial will be reported in a forthcoming paper (unpublished; manuscript in preparation) [25]. In this paper, we present and discuss the rationale and design of a cluster-randomized controlled trial (RCT) that tested the efficacy of a school-based WaSH intervention. The research protocol we describe in this paper was designed and implemented in the Philippines but it can serve as a blueprint for conducting future intervention studies in other LMICs.

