#### 2.8.2. Inferential Statistical Analyses

To address study aims 1 and 3 (Figure 2), we will compare the study arms, using two-sided tests for primary outcomes. For continuous variables, we will use the *t*-test to calculate the mean weight differences between the control and intervention arms. For binary variables, we will use Poisson regression to compare the control and intervention arms according to their relative risk (RR). We will use multiple logistic regression models to analyze exposure-response: g = (E[Ai]) = β0 + β1Bi + γCi, where Ai is the primary outcome of interest, g( )  is the appropriate link function (identity for height and weight, logistic for stunting and poor health literacy), Bi is the continuous exposure of interest, and Ci is the vector of confounders. We describe proposed models in Box S2 and will describe full models in a forthcoming paper [25].

To assess risk factors of health, health literacy, and handwashing outcomes, we will use multiple logistic regression models that account for school-level clustering, estimate precision with 95% confidence intervals (CI), and *p*-values, and produce adjusted odds ratios (aORs). Clustering by school takes into account potential intragroup correlation among children from the same school and enables us to adjust the SE of estimates. aORs control for possible confounders (e.g., children’s age and sex, parent’s educational background and employment status, presence of toilet and handwashing basin inside home, household food insecurity). We will use confounders to calculate an adjusted effect estimate to account for baseline differences between the control and intervention arms. We will use three multiple logistic regression models (Box S2): (1) model A for poor hygiene literacy only, poor handwashing literacy only, and both poor hygiene literacy and poor handwashing literacy; (2) model B for malnutrition, i.e., stunting only, undernutrition only, and overnutrition only; and (3) model C for poor health status only, extreme hunger only, and both poor health status and extreme hunger.

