We will use generalized linear mixed models (GLMMs), which are appropriate for longitudinal data, to determine if the intervention was effective in improving our outcomes of interest. GLMMs are useful for measuring intervention impacts in complex datasets, i.e., when different types of variables (e.g., binary, continuous) are assessed at different time periods, particularly when assessments are made at the group- rather than individual-level. We will use GLMMs to estimate the effect of each intervention compared to the control group. To measure the intervention’s impact, we will estimate differences between pre- and post-intervention outcomes.

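### Section 2.8 gives two unranked tests of the intervention effect, one with no stated allowance for school clustering, and leaves the arm wording and the multiplicity family unsettled

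*Protocol article*

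**What the plan says.** **Arms and contrast.** Section 2.1 states "This was a two-arm cluster-RCT (Figure S1), with one intervention arm and one control arm", and in the same paragraph divides the intervention arm into groups A to D. Section 1.2 (Objectives) says "we will compare a comprehensive school-based WaSH intervention with no intervention". Section 2.5.4 says "We compared differences between control and intervention arms". Section 2.8 opens with "Because our study contains multiple arms (1 control and 4 intervention arms") and refers to five arms. It declines a single global test, adds "Rather we will use a dose-response model to examine trends", and ends its first paragraph by applying intention to treat to all analyses, "comparing each intervention arm against the control arm".

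**Analyses of the effect.** The first paragraph of section 2.8.2 plans two-sided tests of the primary outcomes between study arms: a t-test for continuous variables, and for binary ones "we will use Poisson regression to compare the control and intervention arms according to their relative risk (RR"). Clustering by school first appears in the next paragraph, for the logistic models of risk factors. The last paragraph gives GLMMs the task of deciding whether the intervention was effective: "We will use GLMMs to estimate the effect of each intervention compared to the control group".

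**Outcomes and multiplicity.** Section 2.5.1 lists eight primary variables: two literacy scores, HAZ, BAZ, stunting, undernutrition, overnutrition and handwashing prevalence. Section 2.8 commits to adjusting for several arms and several outcomes. It names the Benjamini–Hochberg procedure (false discovery rate 10%) only as one option, and does not say which tests form the family.

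**The concern.** Two analyses are assigned to the same question, the effect of the intervention on the primary outcomes, and neither is ranked above the other. They are not interchangeable. One is described without any allowance for children in the same school resembling each other; the other is suited to it. In a trial of 15 schools with two controls, that difference can decide whether a result is called significant. If the t-test is positive and the GLMM is not, the article does not say which answer stands.

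The inconsistent arm count makes it harder to tell whether a test labelled control versus intervention pools groups A to D or takes them one at a time. The undefined family means the promised adjustment cannot yet be applied, because the Benjamini–Hochberg thresholds depend on how many tests are counted.

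**Working it through.** **1. Does the sample size show which comparison was meant?** Section 2.3 gives a target of N = 760 from the Lynch formula, a population of 2,059,447 and inflation of 30%, 45% and 5%. Assuming p = 0.5, d = 0.05 and Z = 1.96 (not stated in the article):

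- n0 = N·Z²·p(1−p) / (N·d² + Z²·p(1−p)) = 384.1
- 384.1 × 1.30 × 1.45 × 1.05 = 760.2, against the stated 760

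On these inputs it is the size for estimating one proportion. It points to no between-arm contrast and no model.

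**2. Error rate of an unclustered t-test.** Inputs: 2 control and 13 intervention schools (section 2.5.3) and m = 50 children per school (section 2.3). Assumed: two-sided 5%, and ICC of 0.01, 0.05 and 0.10. The article states neither.

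- True variance of the difference in means: (1/2 + 1/13) × (σ²/m) × [1 + (m − 1)·ICC]
- Variance if clustering is ignored: (1/2 + 1/13) × σ²/m
- Ratio (design effect): DE = 1 + 49 × ICC
- Rejection of a true null: 2 × Φ(−1.96/√DE)

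| ICC | DE | 1.96/√DE | Rejects a true null |
|---|---|---|---|
| 0.01 | 1.49 | 1.606 | 10.8% |
| 0.05 | 3.45 | 1.055 | 29.1% |
| 0.10 | 5.90 | 0.807 | 42.0% |

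Simulation of 15 schools of 50 gave 11%, 29% and 43%. The school counts cancel from the ratio, so with equal school sizes the same inflation applies to an unclustered t-test of any one group against control. The figures are for the t-test; the Poisson comparison was not computed.

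**3. How often the two kinds of test disagree.** A school-level t-test stood in for an analysis that respects clustering. The pooled clustered and unclustered tests gave different verdicts as follows:

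- No effect: 8%, 25% and 37% of simulated trials at ICC 0.01, 0.05 and 0.10.
- Assumed effects of 0.1, 0.2, 0.3 and 0.4 SD in groups A to D: 34%, 44% and 46%.

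These runs assume a 3/3/3/4 split of the 13 schools, because Table S1 is not shown.

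**4. What the promised adjustment would do.** Eight outcomes times four arm contrasts is 32 tests. With Benjamini–Hochberg at 10% over a fixed family, the chance of any false positive when nothing works is about 10% for independent tests (families of 8, 32 and 48 gave the same). It was about 7% for a correlated set of 40 (pooled plus four arm contrasts, eight outcomes). The named method is adequate once its family is fixed.

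**The case against.** The best defence is that the text is loose rather than contradictory. Groups A to D are nested in the intervention arm, so two arms and five groups can describe one design. Section 2.8 states one contrast for all analyses, each arm against control, and section 2.8.2 repeats it for the GLMM. Nothing in section 2.8 says that A to D will be pooled. The phrase about control and intervention arms is plural and is also used in section 2.8 directly after the five arms. The trend model is offered in place of a global test, not as a rival verdict. All of this stands.

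A reader might therefore go too far in three ways:

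- **That pooled, per-arm and trend contrasts compete over 48 candidate tests, with a false-positive chance near 57%.** That figure (outcome correlation 0.5) assumes unadjusted 5% tests, whereas section 2.8 promises adjustment. It also barely reflects the choice of contrast: it is 57.1% without the pooled test and 57.4% with it.
- **That no earlier record limits the analyst, because registration was retroactive.** Section 2.4 says protocols were developed before data collection, and section 2.7 that they were approved by ethics committees. Their content is not shown.
- **That the article must set a pooled gate or a lead outcome.** These are trade-offs usually left to an analysis plan. A pooled gate could also block a single effective group.

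It can also be said that the t-test and Poisson comparisons are tied to aims 1 and 3 in Figure 2, which is not shown, and that Box S2 describes models. That may explain their role. It does not remove the overlap in the text, where both analyses estimate the intervention effect on the outcomes of interest and only one is suited to clustering.

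**Conclusion.** The point holds in limited form. Section 2.8.2 gives two unranked analyses of the intervention effect, and the t-test and Poisson comparison carries no stated allowance for school clustering. If that t-test were read as the answer, its type I error would be about 11% to 42% instead of 5%, for ICC 0.01 to 0.10. This rests on an assumed 5% level, an assumed ICC range, 50 children in every school and a normal approximation. The arm wording is inconsistent, but a deciding contrast can be found in section 2.8. Multiplicity control is promised and the named method would serve; what is missing is commitment to it and a defined family.

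This should be corrected, because the wrong choice between the two analyses could reverse a conclusion. Correcting it does not make the comparison with control randomised: section 2.5.3 says the two control schools were assigned purposefully.

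**What to change.** 1. **Deciding analysis.** State in section 2.8.2 that the GLMM with a school-level effect is the sole deciding analysis of the intervention effect, and label the t-test and Poisson comparisons descriptive. With two control schools the GLMM also needs a small-sample method for its standard errors; the full analysis plan can name it.
2. **Deciding contrast.** Keep the one that section 2.8 already states, each of A to D against control. Align sections 2.1, 2.5.4 and 2.8 with it, and label any pooled comparison supportive.
3. **Multiplicity.** Commit to Benjamini–Hochberg at 10% over a stated family: the eight primary variables by four arm contrasts, 32 tests. Say whether the trend model is inside or outside it.
4. **Timing.** Date the statement and say whether it was made before results were seen. Data collection ended in February 2019 (section 2.1), and section 2.7.2 reports that preliminary results have been presented.

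The cost is wording here and in the results paper, with no new data. The t-test and Poisson results and any pooled result lose confirmatory status. If results had already been seen, the choice must be reported as post hoc.
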